### Sample size calculation

The study is designed as a non-inferiority trial.

The opinion of physicians and experts in malaria treatment has been sought for defining the non-inferiority margin, and this has been set at 5%. In addition, the experts have agreed that, in order for the new treatment to be considered efficacious, its PCR-corrected cure ratio at day 28 should not be lower than 90%. Therefore, in the present trial, dihydroartemisinin-piperaquine will be considered efficacious if both the following conditions are met (see section 2.1):

(i) The PCR-corrected cure ratio at day 28 of dihydroartemisinin-piperaquine is not inferior to the cure rate of artemether-lumefantrine by 5% or more, and independently of the reference drug performance,

(ii) The cure rate of dihydroartemisinin-piperaquine is at least 90%.

In summary, for the non-inferiority analysis, the clinical and statistical specifications for the sample size computations are as follows:

- Primary end point = PCR-corrected cure ratio at day 28.
- Primary analysis = based on 97.5% one-sided confidence intervals for the difference in day 28 cure ratios.
- Alpha = 0.025 (one-sided).
- Power = 80%.
- Cure ratio at day 28 of artemether-lumefantrine = 95% (results from multicentre phase III trial of Coartem in children; [name] personal communication).
- Non-inferiority margin for the difference (test-reference) = -0.05%.
- Analysis will be per-protocol.

To demonstrate non-inferiority of Artekin compared to Coartem the study will require 235 patients per treatment group. To allow for an approximate 5% loss to follow-up rate, 250 patients per treatment group (500 patients in total) will be enrolled in the Kilifi study.

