## Statistical Analysis

### Primary end point analysis

The primary analysis will be based on a 97.5% (one-sided) confidence interval (CI) computed on the difference between the 28-day PCR corrected cure ratios (PP population) of the test and the reference treatments, respectively.

In order to claim that dihydroartemisinin-piperaquine is efficacious, the lower limit of the 97.5% confidence interval of the difference between the treatment groups must be >-0.05 and the point estimate for the 28-day PCR corrected cure ratio of dihydroartemisinin-piperaquine must be >0.90%, in the PP population.

All patients withdrawn from the study will be considered as failures in the ITT population (worst-case scenario).

For computing the PCR-corrected cure ratio, the following rules will be applied:

- The patients with reappearing asexual parasitaemia, which are subsequently found to be due to re-infections are considered as treatment success in both PP and ITT populations;
- The patients for whom the PCR analysis is not interpretable (or blood sample unavailable) are considered as treatment failure in the ITT population, but are excluded from the PP population.

Robustness of results for the primary end point will be investigated by using other analyses, such as the survival analysis techniques.

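### The 235 patients per group do not follow from the listed sample size specifications if the two drugs are assumed equally effective: 80% power needs 299 evaluable per group, and 235 give about 70%

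*Protocol*

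**What the plan says.** Section 10.4.2 (Sample size calculation) presents a list of specifications and then a result. The error rate is "Alpha = 0.025 (one-sided"), and the planned analysis matches it: "Primary analysis = based on 97.5% one-sided confidence intervals for the difference in day 28 cure ratios". Power is 80%. The reference rate is given as "Cure ratio at day 28 of artemether-lumefantrine = 95" per cent. On the margin, expert opinion was sought "for defining the non-inferiority margin, and this has been set at 5" per cent. The analysis is per protocol. The result is "To demonstrate non-inferiority of Artekin compared to Coartem the study will require 235 patients per treatment group", raised for about 5% loss to follow-up so that "250 patients per treatment group (500 patients in total) will be enrolled in the Kilifi study".

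Section 12.3.1 (Primary end point analysis) keeps the same error rate: "The primary analysis will be based on a 97.5% (one-sided) confidence interval (CI) computed on the difference" in PCR-corrected day 28 cure ratios, with the lower limit required to lie above -0.05.

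No section states the cure ratio expected for dihydroartemisinin-piperaquine when the trial was sized, and none mentions a one-sided alpha of 0.05 for the primary comparison.

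**The concern.** A reader who puts the listed specifications into the standard non-inferiority formula, with equal cure ratios, does not get 235. The number is 21% below what comes out (1 - 235/299 = 0.21).

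The stated power is part of the case for the study. Section 10.2 enrols 200 children beyond the multicentre quota, partly so that the Kilifi data can be analysed on their own, and section 13 plans an independent report. If the drugs are truly equal at 95%, the chance of failing to show non-inferiority is about 30% rather than the 20% that the protocol implies. An inconclusive result could then be read as evidence against the test drug when it mainly reflects limited size.

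**Working it through.** **Inputs.** From section 10.4.2: one-sided alpha 0.025 (z = 1.960), power 80% (z = 0.842), reference cure ratio pC = 0.95, margin 0.05, equal groups. One bullet prints the margin as -0.05%. This is a unit slip, since sections 9.1, 12.3.1 and the rest of 10.4.2 give 5% or -0.05, and it does not explain the discrepancy. Assumption, not in the protocol: test cure ratio pT = 0.95.

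**Formula.** n per group = (z_alpha + z_power)² × [pC(1 - pC) + pT(1 - pT)] / [0.05 - (pC - pT)]².

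**Reproducing 235.**
- Listed alpha, pT = 0.95: 7.849 × 0.095 / 0.0025 = 298.3, so 299. The stated figure is not reproduced.
- One-sided alpha 0.05, pT = 0.95: 6.183 × 0.095 / 0.0025 = 234.9, so 235.
- Listed alpha, pT = 0.955: 7.849 × (0.0475 + 0.042975) / 0.055² = 234.8, so 235.
- Other methods at the listed alpha and pT = 0.95 move away from 235: Farrington-Manning gives 334 and a continuity correction 337.

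Two routes therefore lead to 235. One contradicts the stated alpha; the other needs an input that is not stated.

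**Power at one-sided alpha 0.025, both cure ratios 95%.** Power = Phi(0.05 / SE - 1.960), with SE = sqrt(0.095 / n).
- n = 235: SE = 0.02011, Phi(0.527) = 0.701.
- n = 250, all evaluable: SE = 0.01949, Phi(0.605) = 0.727.
- Exact binomial enumeration at 235 per group: 0.706 with a Wald limit, 0.662 with a Newcombe limit. At 250 per group: 0.727 and 0.684.
- Adding the condition that the test cure ratio be at least 90% leaves the exact Wald figure at 0.706.

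**Sensitivity to the unstated test cure ratio** (235 per group, one-sided alpha 0.025):

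| True test cure ratio | Power | n per group for 80% |
|---|---|---|
| 94.5% | 59% | 386 |
| 95% | 70% | 299 |
| 95.5% | 80% | 235 |
| 96% | 88% | 188 |

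**Allowance for loss.** 235 / 0.95 = 247.4, so 248, rounded to 250; this step is sound. The same step from 299 gives 299 / 0.95 = 314.7, so 315 per group.

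**Allocation.** Section 10.4.2 plans 250 per group. Section 10.2 gives 1,000 against 500 for the multicentre trial, and section 11.1.3 uses blocks of 9, which cannot be split equally. If all 500 children were allocated 2:1 (an assumption), then with both cure ratios at 95%:
- 333 against 167, all evaluable: SE = sqrt(0.0475/333 + 0.0475/167) = 0.02067, power 0.677.
- 316 against 158, after 5% loss: SE = 0.02124, power 0.653.

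**The case against.** The strongest reply is that the protocol never says the two drugs were assumed equal. If the planners expected 95.5% for the test drug, then 235 per group gives 80.0% power at the stated alpha and there is no arithmetical error. This stands as a possibility, and it limits the point in two ways. A reader might infer that the trial was sized at one-sided alpha 0.05. The match is exact and equality is the more usual default, but the documents do not show it. A reader might also infer that the design simply has 70% power. That figure holds only if the true test cure ratio is 95%.

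The reply does not clear the section. Its list is offered as the specifications for the computation, and no advantage for the test drug is among them. If one was assumed, a decisive input is missing: half a percentage point either way moves power from 59% to 80%.

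It can also be said that the error is harmless to inference. That is largely right. The confidence limit and the decision rule agree with each other, so a false claim of non-inferiority is no likelier than planned, and the reported interval will show its own imprecision. What is affected is the stated chance of success and the reading of an inconclusive result.

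**Conclusion.** The point holds in conditional form. With a 95% cure ratio in both groups and 1:1 allocation, the listed specifications need 299 evaluable patients per group, and 235 give about 70% power (73% if all 250 are evaluable). No evaluable number within the planned enrolment reaches 80% on that assumption. Either the error rate used for sizing differs from the one stated for the analysis, or a test cure ratio above the reference was assumed and not written down. The documents do not say which. The percentages are normal approximations for unpooled proportions; exact enumeration gives 66 to 71% at 235 per group, depending on the interval method. If allocation is in fact 2:1, which sections 10.2 and 11.1.3 suggest but do not settle for all 500 children, power under equality is lower still, at about 65 to 68%.

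**What to change.** Keep the 97.5% one-sided limit and the 500 children. Replace the sentence giving 235 in section 10.4.2 with:

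*Assuming a true day 28 PCR-corrected cure ratio of 95% in both groups and 1:1 allocation, 235 evaluable patients per group give about 70% power at one-sided alpha 0.025; 80% would require 299 evaluable per group.*

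If a higher cure ratio was assumed for dihydroartemisinin-piperaquine, state it and justify it instead. State the allocation ratio actually used at Kilifi and give the power for it, so that sections 10.2, 10.4.2 and 11.1.3 agree. Do not relax alpha to make 235 fit, because that would contradict section 12.3.1.

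The cost is a sentence or two of text and a less favourable power statement. No patients are added, and neither the analysis nor the decision rule changes. Keeping the 80% claim under equality would instead mean enrolling about 315 per group, 630 in all.

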## Recruitment and trial procedures

The parents or guardians of paediatric patients aged 6-59 months who present to the Pingilikani Health Centre with symptoms suggestive of malaria and a documented, uncomplicated *P. falciparum* infection with an asexual parasite density of 2,000–200,000 parasites/µL, will be informed by the health care facility staff about the ongoing malaria clinical trial. They will be requested to freely consent to let their child participate in the trial. Unwillingness or inability to participate will result in the prescription and administration of the local standard treatment regime for uncomplicated *P. falciparum* malaria (currently 4 mg/kg/day of amodiaquine for 3 days). A screening record will be maintained at the site to log all patients considered as potential subjects into the study, and a recruitment record to log all patients recruited into the study.

The parents or guardians who express interest in participation of their child in the study will receive detailed explanations about the trial from the study staff. Specifically they will be informed that the safety, tolerability and efficacy of two antimalarial drugs will be compared and that their child will be randomly assigned to receive treatment with one of the two drugs (by chance). Finally, they will be asked to sign the informed consent form (see Appendix IV). The study will be explained in the patient’s preferred language (English, Swahili, Giryama), and written informed consent shall be obtained on approved forms (accuracy of translation to be checked by back-translating into English).

At enrolment, children will be assigned a sequential study number. During the first 3 study days (days 0-2) patients will be either be admitted for observation and administration of study medication or managed as outpatients requiring home visits for supervised administration of study drugs at nighttime. Parents/guardians will then be encouraged to return to the clinic for follow up assessments on days 3, 7, 14, 21, 28, 35, 42, 63, and 84 and on any unscheduled day if the child is not well. Compensation for transport to and from the clinic will be provided. All medication will be administered under observation by an authorised member of the study team (physician, clinician, or study nurse).

Standard Operation Procedures (SOP) will be implemented according to international guidelines for the conduct of clinical research (Good Clinical Practice/International Conference on Harmonisation). A Quality Assurance (QA) programme will verify the quality of the trial procedures and data collection. In addition, the study will be independently monitored by a commercial Clinical Research Organisation (CRO; MDS Pharma, South Africa) on a fortnightly basis.

Patients will be assessed as summarized in the following flow-chart.

Table 1. Study Flow Chart of trial assessments and procedures.

|  | **Study days** | | | | | | | | | | | | | | |
| --- | --- | --- | --- | --- | --- | --- | --- | --- | --- | --- | --- | --- | --- | --- | --- |
| **0** | **1** | **2** | **3** | **7** | **14** | **21** | **28** | **35** | **42** | **49** | **56** | **63** | **84** | **Recurrent parasitaemia** |
| **Demographic data/medical history** | x |  |  |  |  |  |  |  |  |  |  |  |  |  |  |
| **Informed consent recording** | x |  |  |  |  |  |  |  |  |  |  |  |  |  |  |
| **Physical examination** | x | x | x | x | x | x | x | x | x | x | x | x | x | x | x |
| **Vital signs and weight1** | x1 | x | x | x | x | x | x | x | x | x | x | x | x | x | x |
| **Blood smear** | x | x | x | x | x | x | x | x | x | x | x | x | x | x | x |
| **Haematology** | x |  |  | x | x | x3 |  | x |  | x |  |  |  | x | x |
| **Clinical chemistry** | x |  |  | x | x2 | x3 |  | x |  | x |  |  |  |  | x |
| **Adverse events recording** | x | x | x | x | x | x | x | x | x | x | x | x | x | x | x |
| **Genotyping sampling** | x |  |  |  |  | x | x | x | x | x | x | x | x | x | x |
| **In vitro adaptation and drug assay** | x4 |  |  |  |  |  |  |  |  |  |  |  |  |  | x |
| **Piperaquine plasma concentration** |  |  |  |  |  |  |  |  |  |  |  |  |  |  | x6 |
| **Detection of subpatent asexual parasitaemia** |  |  |  |  | x7 | x7 |  |  |  |  |  |  |  |  |  |
| **Study of *var* gene expression** | **x** |  |  |  |  |  |  |  |  |  |  |  |  |  | **x** |
| **Concomitant treatments recording** | x | x | x | x | x | x | x | x | x | x | x | x | x | x | x |
| **Study medications** | x | x | x |  |  |  |  |  |  |  |  |  |  |  |  |

1. Weight will be measured at day 0

2. If abnormal at day 3

3. If abnormal at day 7

4. Using isolates from 50 randomly selected patients

5. If abnormal on day 28

6. Corresponding number of samples will be obtained from control (asexual parasite free) patients

7. Retrospective analysis only in case of recurrent recurrent asexual parasitaemia using samples taken for haematology

### Study visits

In the event of a suspected adverse drug reaction (irrespective of the day upon which this is noted) the physician shall seek permission to draw a venous blood sample, which will be used for a full blood count and biochemistry analysis.

#### Day 0: Screening/Treatment phase

1. Informed Consent

A signed informed consent from the parent/guardian shall be obtained before any tests or evaluations related to the study eligibility are carried out.

1. Demographic Data and Medical History

Demographic data and a general history of past and present illnesses will be recorded.

1. Physical and Clinical Examination

A general physical examination will be performed (see Appendix I).

A clinical examination will be performed (see Appendix I): symptoms, axillary or tympanic temperature (electronic thermometer). Weight and height will also be measured.

1. Vital Signs

Vital signs (systolic and diastolic blood pressure, heart rate).

1. PCR

A blood sample will be collected on filter paper (grade 1) for parasite genotyping.

1. Blood Slide

A thick and thin blood smear will be obtained from the subject to verify the presence of *P. falciparum* and to determine asexual and sexual parasite densities. Thick and thin blood films will be prepared, dried and stained with Giemsa stain according to standard operating procedures.

Parasite density will be calculated by counting the number of asexual parasites per 200 leukocytes in the thick blood film, based on an assumed leukocyte count of 8,000 /µl by light microscopy at 1000x magnification. One hundred high-powered fields (HPF) will examined (independent of presence or absence of asexual parasite stages). The parasite density per µL will be calculated using the following formula: numbers of parasites/µl = number of parasites counted x 8,000/number of leukocytes counted

1. Laboratory Tests

Blood haemoglobin, red blood cell count, total leukocyte count, differential count (neutrophils, basophils, eosinophils, monocytes, lymphocytes) and platelet count.

Total bilirubin, ALT and creatinine will be measured. **Parasite RNA will be analysed for variant gene expression patterns.**

1. Administration of the study drugs

For details see chapter 7 (Investigational product(s) & concomitant medications and non-drug therapies).

#### Day 1: Treatment phase

1. Physical and Clinical Examination

A general physical examination and a clinical examination will be performed: symptoms, axillary or tympanic temperature (electronic thermometer).

1. Vital Signs

Vital signs (systolic and diastolic blood pressure, heart rate) will be measured.

1. Blood Slide

A thick and thin blood smear will be obtained to verify the presence and to determine the density of asexual and sexual stages of *P*. *falciparum*.

1. Concomitant Pharmacological Treatments

Concomitant medications being taken by the patients will be recorded. For a list of allowed and disallowed medications, see section 4.

1. Adverse Events Report

The start and end of clinical adverse events will be recorded.

1. Administration of the study drugs

#### Day 2: Treatment phase

1. Physical and Clinical Examination

A general physical examination and a clinical examination will be performed: symptoms, axillary or tympanic temperature (electronic thermometer).

1. Vital Signs

Vital signs (systolic and diastolic blood pressure, heart rate) will be measured.

1. Blood Slide

A thick and thin blood smear will be obtained to determine the presence and the density of asexual and sexual stages of *P*. *falciparum*.

1. Concomitant Pharmacological Treatments

Concomitant medications being taken by the patients will be recorded. For a list of allowed and disallowed medications, see section 4.

1. Adverse Events Report

The start and end of clinical adverse events will be recorded.

1. Administration of the study drugs

#### Day 3: Follow-up phase

1. Physical and Clinical Examination

A general physical examination and a clinical examination will be performed: symptoms, axillary or tympanic temperature (electronic thermometer).

1. Vital Signs

Vital signs (Systolic and Diastolic Blood Pressure, Heart Rate) will be collected.

1. Blood Slide

A thick and thin blood smear will be obtained to determine the presence and the density of asexual and sexual stages of *P*. *falciparum.*

1. Concomitant Pharmacological Treatments

Concomitant medications being taken by the patients will be recorded. For a list of allowed and disallowed medications, see section 4.

1. Adverse Events Report

The start and end of clinical adverse events will be recorded.

1. Laboratory Tests

Blood haemoglobin, red blood cell count, total leukocyte count, differential count (neutrophils, basophils, eosinophils, monocytes, lymphocytes) and platelet count.

Total bilirubin, ALT and creatinine will be measured.

#### Day 7: Follow-up phase

During this visit, the same procedures as the visit 4 will be applied. EDTA and RNA samples will be taken for haematology and detection of subpatent parasitaemia, respectively. Laboratory tests will be performed in case of abnormality at D3.

#### Days 14 and 21: Follow-up phase

During these visits, the same procedures as the visit 4 will be applied.

A blood sample will be collected on filter paper (grade 1) for parasite genotyping **and a RNA sample for detection of subpatent parasitaemia.**

Laboratory tests will be performed at D14 in case of abnormality at D7.

#### Day 28: Follow-up phase

1. Physical and Clinical Examination

A general physical examination and a clinical examination will be performed: symptoms, axillary or aural temperature (electronic thermometer).

1. Vital Signs

Vital signs (Systolic and Diastolic Blood Pressure, Heart Rate) will be collected.

1. Blood Slide

A thick and thin blood smear will be obtained to determine the presence and the density of asexual and sexual stages of *P*. *falciparum.*

Filter paper for PCR analysis.

1. PCR

A blood sample will be collected on filter paper (grade 1) for parasite genotyping.

1. Laboratory Tests

Blood haemoglobin, red blood cell count, total leukocyte count, differential count and platelet count.

Total bilirubin, alanine aminotransferase (ALT) and creatinine will be measured.

The Investigator(s) will check all laboratory tests results and report them onto the Case Report Form (CRF) and will indicate those with potential clinical relevance. An abnormal laboratory test value of potential clinical relevance will be reported using the Adverse Event Form attached to the CRF.

1. Concomitant Treatments

Concomitant medications being taken by the patients will be recorded. For a list of allowed and disallowed medications, see section 4.

1. Adverse Events Report

The start and end of clinical adverse events will be recorded.

#### Days 35, 42, 49, 56, 63, and 84: Follow-up phase

During this visit, the same procedures as on days 14 and 21 will be performed.

However, haematology will be done on days 42 and 84 PCR on all days **and parasite RNA analysed for variant gene expression pattern**.

### Blood sampling

2 mL is required for each biochemistry assessment, 3 ml drug assays (piperaquine, lumefantrine, dihydroartemisinin) in a subset of patients, 1.2 mL for haematology, 1.6 ml for detection of subpatent asexual parasitaemia on days 7 **and 14**, 0.8 ml for parasite RNA at baseline, 2 ml for determination of piperaquine plasma level at asexual parasite reappearance, 50 µL for parasitology, and 50 µl for parasite genotyping. Thus, the total (maximum) blood volume collected per patient over a period of 84 days (approx. 3 months) should not exceed 26.8 ml and will average 18.0 ml (divided into 7 samples). Drug assays will be carried out as part of [name] project. Detailed information regarding this project will be submitted in parallel for clearance to the Ethics and Scientific Committees under the title: `Understanding the mechanisms of the antimalarial piperaquine resistance´.

### Parasite genotyping

Fifty µl of capillary blood obtained by finger stick will be spotted onto filter paper (labelled with study number of patient, study day and date) and dried before sealing it in a plastic bag. Each specimen will be recorded in a specimen logbook and stored at room temperature. The date of dispatch of all specimens will also be recorded. Pairs of parasite isolates from day 0 and day of recurrent asexual parasitaemia will be subjected to genotyping analysis to distinguish recrudescent from new infections. We will use a standard protocol based on the amplification and subsequent size differentiation via gel electrophoresis of three polymorphic *P. falciparum* genes: merozoite surface proteins-1 and –2 genes (*msp1* and *msp2*) and the glutamate-rich protein (*glurp*) gene. In addition, we will apply microsatellite analysis to confirm the results of the standard parasite genotyping approach described above [26].

